## Abstract

**Background:**

An exclusive breastfeeding rate in the first 6 months of life of at least 50% is one of the six World Health Organization global nutrition targets for 2025. However, the exclusive breastfeeding rate in China is quite low and decreasing which makes it urgent to explore effective ways to reverse the current downward trend. As mobile technologies have rapidly developed, mobile communication apps such as WeChat (one of the largest social networking platforms in China) are well accepted and have the potential to improve health behaviors in a convenient way. The current paper describes the study protocol of a WeChat intervention that aims to promote breastfeeding in rural areas in China.

**Methods:**

The study is designed as a randomized controlled trial in rural Qinghai Province, China. Women who are 14–36 weeks pregnant will be randomized to routine antenatal and postnatal care, or routine care plus the WeChat breastfeeding education. pregnant women with a severe disease and complications of pregnancy or HIV-1 will be excluded. Breastfeeding knowledge and promotion information will be delivered to the intervention group through a WeChat official account from 3 months pregnancy to 6 months postpartum. The outcome assessments are conducted at baseline through face-to-face interviews, and at one week, 1 month, 3 months and 6 months postpartum by telephone interviews. The primary outcome is difference in the exclusive breastfeeding rate at 1 month, 3 months, and 6 months postpartum between the intervention group and the control group. Secondary outcomes include the overall duration of any and exclusive breastfeeding across the first 6 months postpartum; mothers’ knowledge of breastfeeding; the proportion of early initiation of breastfeeding; and the timing of the introduction of solid food to infants. Intention-to-treat-analysis will be used. Survival analysis will be used to compare the overall duration of any and exclusive breastfeeding between groups.

**Discussion:**

This study is the first effort to promote exclusive breastfeeding through WeChat in China. Our results will provide scientific evidence for the effect of health education through WeChat on breastfeeding. Thereby this may offer a comprehensive intervention to promote exclusive breastfeeding in China and other settings.

**Trial registration:**

Chinese Clinical Trial Registry –ChiCTR1800017364. Registered 26 July 2018. http://www.chictr.org.cn/showproj.aspx?proj=29325

## Background

Increasing the exclusive breastfeeding rate in the first 6 months of life to at least 50% is one of the 6 WHO global nutrition targets for 2025 [1]. The benefits of breastfeeding for both infants and mothers have been well recognized [2]. Exclusive breastfeeding provides infants with the best start to life by ensuring adequate nutrition and protection from infection, as well as fostering early growth and development. Therefore, the World Health Organization (WHO) and United Nations Children’s Fund (UNICEF) jointly recommend that infants should be exclusively breastfed for six months after birth, and be continuously breastfed to 2 years or beyond [3].

Over the past two decades, China has adopted the WHO’s feeding recommendations and implemented programs to promote breastfeeding and complementary feeding, such as the infant and young child feeding (IYCF) guidelines and the integrated management of childhood illness (IMCI) guidelines [4–6]. Moreover, China initiated a national Basic Public Health Service program in 2009 to provide universal basic public health services for all residents [7], for which maternal and child health care workers are required to provide face-to-face counseling to women during antenatal care visits, hospital delivery, newborn home, postnatal care and child health care visits [7]. Nevertheless, exclusive breastfeeding under six months in China is still suboptimal; the latest national Chinese data from 2013 showed that the exclusive breastfeeding rate under six months was only 18.6% [8], which was even lower than the rate in 2008 (27.6%) [9]. Research studies have also reported a range of low exclusive breastfeeding rates under six months in China: 28.7% in central and western China [10]; and 9.7% in a rural county in Northern China [11]. Recent data showed that the exclusive breastfeeding rate in infants younger than 6 months was 41% globally [12] and 37% in low-income or middle-income countries [2]. As the exclusive breastfeeding rate in China was even lower than the global average level, much effort is needed to promote breastfeeding, especially exclusive breastfeeding.

Breastfeeding practices are influenced by a wide range of socio-economic, cultural, and individual factors in China, including maternal age, illness, delivery patterns, premature delivery, lactation factors, food intake before breastfeeding, infant’s sucking ability, the mother’s milk supply, the intention to breastfeed, understanding of breastfeeding benefits, breastfeeding experience, returning to work, and family support [13–16]. The most successful interventions to promote exclusive breastfeeding contain education and support, which are the two main approaches to breastfeeding promotion [17]. Successful breastfeeding depends on antenatal and postnatal breastfeeding education and on the support provided by healthcare professionals [14]. Improved breastfeeding knowledge and attitudes toward breastfeeding are related to more positive breastfeeding outcomes. However, our previous data from a rural county in northern China suggested that only 37.3% mothers knew the accurate duration of exclusive breastfeeding, and fewer than 30% of mothers ever received feeding information during pregnancy or after delivery [12]. Moreover, around 80% of mothers’ sources of information were family members, neighbors, friends and popular media (newspaper, magazine, book, radio and television), rather than health facilities [12]. As health workers in health facilities only have limited time and resources to provide breastfeeding education, there is a great need to explore other approaches to deliver breastfeeding education and support to mothers.

Smartphones have become new channels and tools for information acquisition and exchange, and been enthusiastically adopted by the general public. Among instant-messaging apps for smartphones, WeChat (the Chinese name is *Weixin*) is regarded as one of the largest social networking platforms in China. WeChat is a free all-in-one communications app widely used for sending text and voice messages, video calls, sharing photos and ‘moments’ (updates on someone’s daily life), and playing games [18]. Since first launched in January 2011, there are more than one billion registered WeChat users throughout the world by the end of 2018 [18]. In 2018, WeChat gradually attracted nearly 902 million daily active users [18]. Furthermore, there is a popular functional module of WeChat called ‘WeChat official accounts’, which can be requested for free and used to disseminate information. WeChat users can subscribe to official accounts and receive selected news or information. Currently, the number of registered WeChat Official Account has reached 20 million [19]. WeChat has been used as a communication tool and been shown to positively impacts on changing selected health behaviours. Using a WeChat account as part of treatment and management of asthma can help patients to learn about their disease and medications, as well as improve disease control and therapy outcomes [20]. A health education intervention via a WeChat account proved to be an effective, sustainable, feasible, and well-accepted strategy for improving malaria health literacy among Chinese expatriates in Niger [21]. A WeChat account used to carry out a weight loss intervention showed that the more actively male participants used WeChat, the more weight they lost [22]. To our knowledge, no previous study has evaluated the effects of WeChat education on breastfeeding promotion. Therefore, we aim to undertake a randomized control trial to evaluate the effectiveness of a WeChat education intervention in improving the exclusive breastfeeding rate and the duration of exclusive breastfeeding in rural areas of China.

## Methods

### Design

This randomized controlled trial (RCT) will evaluate the effectiveness of using the official WeChat account called “Huzhu County Maternal and Child Health Family Planning Service Centre” in improving exclusive breastfeeding of children aged 0–6 months in rural Qinghai Province, China. Women pregnant 14–36 weeks will be randomized to routine antenatal and postnatal care or routine care plus the WeChat breastfeeding education (Fig. 1). Breastfeeding knowledge and promotion information will be delivered to the intervention group through the WeChat official account to women from the third month of their pregnancy until six months postpartum. The sampling unit is individual pregnant woman and we will enroll 200 pregnant women for both intervention and control group, respectively.

**Fig. 1 Fig1:**
[figure not shown]
Study protocol flowchart of breastfeeding health education via an official WeChat account

### Study area

This trial will be conducted in Huzhu County, Qinghai Province, China. Qinghai province lies in northwest China, with a surface area of 720,000 km^2^. By the end of 2017, the total population was 5,838,000 of which the rural population accounted for 46.9%. Qinghai Province has 34 counties and 439 townships. Huzhu County lies in the northeast of Qinghai province, with a surface area of 3423.9 km^2^. The county has a total population of 401,540 of which the rural population accounts for 76.0% and more than 80% people were Han Chinese. People in Huzhu County mainly make a living by farming. The annual per capita income of rural residents was Ұ9810 (US$1414.91) in 2017 [23]. In addition, there were a total of 91,321 women at reproductive ages and 4325 pregnant women in 2017.

Huzhu County has 19 townships, with 294 villages, of which we will select 13 townships as our study areas. Six townships will be excluded because whilst planning this study, 4 townships had already been selected by another maternal and child health project and another 2 townships are remote and only have a small number of pregnant women.

### Participants

We will enroll women who are 14–36 weeks pregnant from 13 townships in Huzhu County as our participants. Eligibility inclusion criteria will be: 1) first-time mothers aged 18 years old or above; 2) 14–36 weeks pregnant and conceiving a singleton fetus; 3) no known illness that limits breastfeeding after childbirth; 4) no long-term plan to go out of the county in the following year; 5) no plan to change their mobile phone number in the following year; 6) can read and communicate in Mandarin, use WeChat through smartphones, and have access to the internet; 7) informed consent and willing to cooperate actively. Participants with the following characteristics will be excluded: 1) pregnant women with a severe disease and complications of pregnancy, such as cerebrovascular diseases, pneumonia and threatened abortion; 2) pregnant women with HIV. Postpartum exclusion criteria will be: 1) mothers developing health complications after birth, such as acute uterine inversion, post partum hemorrhage or post partum depression; 2) infants who are admitted to the neonatal intensive care unit, have a 1-min Apgar score < 6, 5-min Apgar score < 6, low birth weight (< 2500 g), or were born prematurely (< 37 weeks of gestation); 3) infants who are diagnosed with a cleft palate or other congenital abnormality that will prohibit breastfeeding; 4) mothers and infants who move out or do not live in Huzhu County after birth.

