### Recruitment and randomization

Before the baseline survey, each township hospital will firstly provide a list of names of all women who are 14–36 weeks pregnant of their own township, which also includes information on gestational age, gravidity and parity. In addition, we will ask the township hospitals to highlight on the list pregnant women who are not at home all the year, do not receive antenatal care in township hospitals, or are unable to use a smartphone. Based on the inclusion and exclusion criteria, they will be asked to come to their own township hospitals. Those who meet the eligibility criteria will be given full information about the study. After signing the written informed consent and completing a basic demographic questionnaire, all the eligible participants will be randomized to either the WeChat intervention group or the control group at a 1:1 ratio.

An independent statistician who will not participate in recruitment or data collection will generate 400 random numbers using Microsoft Excel. She will use the median of the random numbers as a threshold. Random numbers lower or equal to the median will be allocated to the intervention group and random numbers higher than the median will be allocated to the control group. The random numbers and the allocated group will be printed on small cards, and kept in opaque, sealed envelopes. At the back of the random number card, the two-dimensional codes of the WeChat official account “Huzhu County Maternal and Child Health Family Planning Service Centre” will be printed. In addition, the two-dimensional code of “Assistant 1” will also be printed at the back of the random number card for intervention group and “Assistant 2” for control group. “Assistant 1” and “Assistant 2” will be used by study team members for future follow-up.

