### Data management and analysis

One research staff member blinded to the treatment allocation will be in charge of database maintenance and management. Logic verification statements will be written in data acquisition software for the smartphone. Baseline data and follow-up data will be saved first on the smartphone, and then wirelessly uploaded into an Excel database via an internet server [29].

Statistical analyses will be performed by the research staff using SAS 9.2 software (SAS Institute, Cary, NC). Continuous variables will be presented as mean and deviation, while categorical variables as numbers and proportions. The homogeneity in baseline characteristics between the intervention group and control group will be estimated using t tests for continuous variables andχ^2^ test for categorical variables. In addition, theχ^2^ test will also be used to compare the differences of exclusive breastfeeding rate between two group at one week, 1 month, 3 months, and 6 months postpartum. Survival analysis will be used to compare the overall duration of any and exclusive breastfeeding between the groups. We will construct Kaplan-Meier survival curves to estimate the median exclusive breastfeeding times and use the log-rank test to compare the differences. We will also perform Cox proportional hazards regression to estimate hazard ratios for stopping exclusive breastfeeding or any breastfeeding.

The principle of intention-to-treat-analysis will be used. This means that participants who drop out or are lost to follow-up during the postpartum period will be considered to have stopped breastfeeding at the point of the last follow-up contact and all randomized participants will be included in the analysis. We will further calculate the odds ratios of any and exclusive breastfeeding at each follow-up time point using logistic regression. All statistical tests will be two-tailed and *P* < 0.05 will be considered significant.

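### Postpartum exclusion criteria remove women after randomisation, contradicting the stated intention-to-treat analysis and exposing the primary comparison to bias

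*Protocol article*

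**What the plan says.** **Randomisation is antenatal.** Design: "Women pregnant 14–36 weeks will be randomized to routine antenatal and postnatal care or routine care plus the WeChat breastfeeding education". Recruitment and randomization: "all the eligible participants will be randomized to either the WeChat intervention group or the control group at a 1:1 ratio", after consent and the baseline questionnaire.

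**Exclusions are postnatal.** Participants gives a separate list of postpartum criteria, which opens "Postpartum exclusion criteria will be: 1) mothers developing health complications after birth". Its items are:
- maternal: "mothers developing health complications after birth, such as acute uterine inversion, post partum hemorrhage or post partum depression";
- infant condition: "infants who are admitted to the neonatal intensive care unit, have a 1-min Apgar score < 6, 5-min Apgar score < 6, low birth weight", or birth before 37 weeks;
- malformation: "infants who are diagnosed with a cleft palate or other congenital abnormality that will prohibit breastfeeding";
- residence: "mothers and infants who move out or do not live in Huzhu County after birth".

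**The analysis keeps everyone.** Data management and analysis adopts intention to treat, counts women who drop out or are lost as having stopped breastfeeding at last contact, and states that "all randomized participants will be included in the analysis".

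**Other relevant statements.** Follow-up is by telephone at week 1 and months 1, 3 and 6 (Data collection). The increase from 93 to 200 women per arm is attributed to refusal and loss to follow-up only (Sample size calculation).

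**The concern.** Every postpartum criterion is observed after allocation, and the education starts in pregnancy. If these women leave the analysis, it is not intention to treat, and randomisation no longer guarantees that the arms compared are alike.

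Several criteria bear directly on the primary outcome: a malformation that rules out breastfeeding is named as one, and admission to intensive care and prematurity also make exclusive breastfeeding less likely. Removing such women raises the observed rate, and removing more of them from one arm shifts the comparison.

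A difference between arms is possible. Mothers learn their arm by opening the envelope themselves, and the team follows them up through Assistant accounts that differ by arm (Recruitment and randomization). Intervention mothers also have an expert forum, through which problems may come to notice. Postpartum depression and moving away have no time limit, so an exclusion could be made after feeding status has been recorded.

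**Working it through.** **1. The two rules applied to the same woman**

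- *Preterm infant, mother answers every call and is still breastfeeding exclusively.* Under Participants she is excluded. Under Data management and analysis she is included with her observed outcome.
- *Mother moves away and is lost.* Under Participants she leaves the denominator. Under Data management and analysis she counts as having stopped.
- *Mother moves away but answers the telephone.* She is excluded under one section and observed under the other. Moving does not in itself end telephone follow-up, and women planning to change their number are not enrolled.

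Two analysts following this text could build different primary data sets. This conclusion needs no arithmetic.

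**2. The plan's sample size**

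Inputs from Sample size calculation: p₁ = 0.292; a 20% increase read as 20 percentage points, so p₂ = 0.492; power 80%; 5% significance level (two-sided, per Data management and analysis). The mean proportion is p̄ = 0.392.

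n = [1.96·√(2·0.392·0.608) + 0.8416·√(0.292·0.708 + 0.492·0.508)]² / 0.20² = (1.353 + 0.569)² / 0.04 ≈ 92.4, rounded up to **93 per arm**. The stated figure reproduces.

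**3. Bias when excluded women are removed (no true effect)**

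The documents give no exclusion rates, so those below are assumed. With overall rate p, excluded fraction x and rate q among excluded women, the rate observed in those who remain is (p − x·q)/(1 − x). Here p = 0.292 in both arms and 200 women are randomised per arm. Type I error uses a normal approximation.

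| Excluded, control v intervention | q | Observed rates | False difference | Type I error |
|---|---|---|---|---|
| 10% v 10% | 0 | 32.4% v 32.4% | 0 | 5% |
| 10% v 10% | 10% | 31.3% v 31.3% | 0 | 5% |
| 10% v 15% | 0 | 32.4% v 34.4% | 1.9 points | about 6.7% |
| 10% v 15% | 10% | 31.3% v 32.6% | 1.3 points | about 5.7% |
| 10% v 20% | 0 | 32.4% v 36.5% | 4.1 points | about 12% |
| 10% v 20% | 10% | 31.3% v 34.0% | 2.7 points | about 8.2% |

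The result depends on the base rate. With an assumed 40% in both arms and q = 10%, excluding 20% v 10% gives (0.40 − 0.02)/0.80 = 47.5% v (0.40 − 0.01)/0.90 = 43.3%, a false difference of 4.2 points.

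**4. Cost of keeping everyone**

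- *12% of each arm meet the criteria, 10% of them breastfeed exclusively.* Control: 0.88·0.292 + 0.12·0.10 = 0.269. Intervention: 0.88·0.492 + 0.12·0.10 = 0.445. The difference is 17.6 points. Power with 200 per arm is Φ[(0.176·√200 − 1.96·0.678)/0.666] = Φ(1.74), about **96%**.
- *None of the women meeting the criteria breastfeed exclusively.* If 5%, 10%, 20% or 30% of each arm meet them, the effect is 19, 18, 16 or 14 points and power is 97.8%, 96.7%, 93.5% or 88.3%. With no such women it is 98.5%.

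**The case against.** **Exclusion might mean only the end of follow-up, not removal from the analysis.** The article does not say which. On that reading all randomised women stay in, but a reachable mother who is still breastfeeding is recorded as having stopped at last contact. That is a different error, and the text remains unreconciled.

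**Differential exclusion is unproven.** Most criteria are facts of delivery or of the medical record. Breastfeeding education is unlikely to change birth weight, Apgar score, prematurity or malformation. The forum is for breastfeeding questions, and no depression screening is described. Women planning a long absence are already ineligible. The Discussion promises methods to blind data collection, and the database manager is blinded. Much of this stands: the plausible arm-related routes are depression and residence. The blinding methods are not described, however, and the arm-specific Assistant accounts work against them. The article does not say who applies the exclusions.

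**The larger illustrations are extreme.** Excluding 40 v 20 of 200 would itself be a marked imbalance (chi-square about 7.8, p about 0.005), and balanced exclusion gives no false difference under the null. Both points are right. The bias figures show what could happen, not what is expected.

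**A declared modified intention-to-treat set is another repair**, with exclusions decided blind to arm and reported by arm. It would remove the contradiction, but it would no longer be the analysis of all randomised women that the plan claims.

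**Conclusion.** The concern holds, and this must be fixed. The plan excludes women on events after randomisation and also says that all randomised women are analysed. The primary analysis set is therefore not fixed, and the intention-to-treat claim fails if the exclusions are applied as written.

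The contradiction rests on the text alone. The size of any bias cannot be derived from the documents. At the protocol's 29.2% rate, with 0 to 10% exclusive breastfeeding among excluded women, it runs from zero when exclusions are balanced, through 1.3 to 1.9 points at 10% v 15%, to 2.7 to 4.1 points at 10% v 20%. Even balanced exclusion raises both reported rates, by 2.1 to 3.2 points at 10% excluded, and changes the population described.

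Power is not the issue. Removing 20% of each arm would still leave 95.9%, and keeping everyone is also affordable.

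**What to change.** 1. State under Participants that the postpartum criteria remove no woman from follow-up or from the primary analysis.
2. State under Data management and analysis that every randomised woman is followed and analysed in her allocated arm, with her observed outcome wherever she can be reached. Say how the outcome is assigned when breastfeeding is impossible, such as a malformation that rules it out.
3. Use the postpartum criteria only to define a secondary (per-protocol or sensitivity) set. Judge them blind to arm where possible, and report counts by criterion and arm.
4. Delete moving out of the county as an exclusion and keep telephoning these mothers.

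The cost is a change of wording, a few more telephone interviews and a modest dilution of the effect (20 to 17.6 points in the 12% example). The planned 200 per arm, against a required 93, absorbs it.
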